## Abstract

**Background:**

Cardiovascular disease (including coronary heart disease and stroke) is a major cause of death and disability in the United Kingdom, and is to a large extent preventable, by lifestyle modification and drug therapy. The recent standardisation of electronic codes for cardiovascular risk variables through the United Kingdom's new General Practice contract provides an opportunity for the application of risk algorithms to identify high risk individuals. This randomised controlled trial will test the benefits of an automated system of alert messages and practice searches to identify those at highest risk of cardiovascular disease in primary care databases.

**Design:**

Patients over 50 years old in practice databases will be randomised to the intervention group that will receive the alert messages and searches, and a control group who will continue to receive usual care. In addition to those at high estimated risk, potentially high risk patients will be identified who have insufficient data to allow a risk estimate to be made. Further groups identified will be those with possible undiagnosed diabetes, based either on elevated past recorded blood glucose measurements, or an absence of recent blood glucose measurement in those with established cardiovascular disease.

**Outcome measures:**

The intervention will be applied for two years, and outcome data will be collected for a further year. The primary outcome measure will be the annual rate of cardiovascular events in the intervention and control arms of the study. Secondary measures include the proportion of patients at high estimated cardiovascular risk, the proportion of patients with missing data for a risk estimate, and the proportion with undefined diabetes status at the end of the trial.

## Background

### Primary research question

Can an automated system of electronic feedback (e-Nudge) reduce the incidence of cardiovascular events in high risk patients in general practice, compared to "usual care"?

### Background

A major focus of chronic disease management is the prevention of cardiovascular disease (CVD). An important development occurred in UK primary care in April 2004, with the introduction of the "new General Medical Services Contract" (nGMS) [1]. This involved the establishment of registers for a number of conditions relevant to CVD prevention, and the resulting standardisation of electronic record keeping has made the data potentially useful for research [2]. The Quality and Outcomes Framework (QOF) of the nGMS specifies targets for blood pressure, serum cholesterol levels, and smoking cessation advice for patients with hypertension, diabetes, or established CVD. Whilst not included in the QOF, the Coronary Heart Disease (CHD) National Service Framework (NSF) [3] also recommends the systematic identification of patients at high risk of CHD but who are not yet displaying any symptoms.

For many patients, the need for preventive treatment is clear, for example through a diagnosis of CVD or diabetes, but for others, the overall cardiovascular risk should be taken into account when determining the need for treatment of hypertension or hypercholesterolaemia. This strategy is strongly supported by the recently published Joint British Societies guidelines on prevention of CVD in clinical practice [4]. This project will assess the effectiveness of targeting patients who are the most likely to benefit from risk factor modification on the basis of their absolute risk of cardiovascular events.

### Changing clinical behaviour through electronic reminders

Despite increasing use of electronic reminders and alert messages, there are relatively few controlled trials that demonstrate their ability to modify clinical behaviour, and none so far carried out in the UK under the new General Practice contract. Published literature is largely concerned with the following uses of these tools:

• to increase physician or nurse adherence to guidelines on best practice in the clinical environment [5], including the use of drug therapy [6]

• to increase the uptake of vaccinations [7-11]

• to promote other preventive health care activities, by triggering opportunistic interventions including screening [12], monitoring [13,14], diagnostic tests [15], and lifestyle counselling [16,17]

• to increase the cost-effectiveness of health care, by avoiding duplication, facilitating communication between members of the health care team [18], and reducing the need for recall of patients through increased use of opportunistic activities during consultations

Of these, the most successful area is vaccination uptake, where a number of studies have demonstrated benefit [7-10], and in the avoidance of prescribing errors, where alerts have been shown to be effective in decreasing the ordering and administration of contraindicated drugs, for instance due to renal insufficiency [19].

Results in other areas have been mixed [20], and may depend on the response of the clinician to the alert message, which must therefore be appropriately designed [21]. In a United States outpatient clinic setting, Tierney et al [22] tested the effects of a system of electronic 'suggestions' for cardiac care patients through a randomised controlled trial, and failed to demonstrate any control-intervention differences in quality of life, medication compliance, health care utilisation, costs, or satisfaction with care. The intervention had no effect on physicians' adherence to the care suggestions. However in Italy, electronic reminders have been shown to be effective in modifying prescribing behaviour. Filippi et al [23] investigated the effects of computerised reminders plus a letter describing the beneficial effects of anti-platelet therapy (intervention group) with the letter alone (controls) among 300 Italian general practitioners randomised to each group. The number of treated patients was significantly raised in the patients of the intervention group (OR 1.99, 95% CI 1.79 – 2.22).

In Scotland, the CARDIA (Computerised Automated Risk Detection Intervention and Advice) program [24] serves practices throughout Angus using a similar system of database integration as that proposed in this e-Nudge study. CARDIA interrogates the electronic health record (EHR), which uses information from both primary and secondary care sources. CARDIA targets resources by examining the practices' EHRs, identifying patients with existing cardiovascular disease (or those at high risk of it based on a Framingham calculation), and assesses the adequacy of care (e.g. drug therapy) in individual patients. However the effectiveness of this program has not been formally tested in a clinical trial.

In secondary care, Lilford et al [25] have described (but not evaluated) a system of electronic reminders for use in the antenatal clinic. This system supplies action suggestions during the antenatal booking interview, as a complement to individual clinical judgement. Eighty-two different suggestions were included in the software, and on average 1.5 of these were generated in an individual history. The authors emphasise the potential for such systems to be adapted to the resources and preferences of different hospitals.

### Controlled studies similar to the e-Nudge trial

One randomised controlled trial in primary care [26] has assessed the effectiveness of electronic feedback using off-line data analysis followed by a flag in the electronic health record. Randomisation was at the health professional level. The outcome was the proportion of patients under the care of each professional still eligible for an alert a month later. This design is in some ways similar to this e-Nudge trial, and the result was positive, but it took place in the USA and only involved one cycle of data analysis with follow-up one month later. In secondary care, the effectiveness of a similar intervention aimed at clinicians caring for hospital inpatients at risk of deep vein thrombosis (DVT) was more dramatically demonstrated [27]. In this case randomisation was at the individual patient level and the outcome was the actual development of DVT. The intervention group patients were found to have a 40% reduced rate of thrombosis compared with controls. A similarly-designed study of electronic reminders for the improved care of patients with HIV infection achieved a significant reduction in hospitalisation in the intervention group [28].

Mitchell et al [29] used information extracted from Scottish general practices to target care towards those aged 65–79 years most in need of intervention for their blood pressure. Information was extracted annually, and 54 practices were cluster-randomised into three groups: those receiving feedback of information identifying patients with uncontrolled blood pressure, those receiving the same feedback but including patients' estimated absolute cardiovascular risk, and control practices receiving no feedback. Whilst reductions in the proportion of patients with controlled blood pressure were seen, the results were compromised by difficulties in stratification according to practice characteristics (resulting in an excess of controls that were training practices, and having a hypertension recall system).

Evidence published to date suggests that the benefits of electronic reminders are context-dependent, relying not only on the area of care involved, but also on organisational parameters, clinical targets, and medicolegal implications. A Veterans Health Administration study [30] demonstrated significant variation in the implementation of electronic reminders including their greater use for conditions associated with performance measures. Agarwal et al [31], in a study of 15 different computerised reminders found that while overall adherence was high, there is significant variation by clinic, individual clinician and individual reminder. For instance, the hepatitis C risk assessment reminder was found to have the highest overall adherence rate (95.9%) and the tobacco use cessation had the lowest adherence rate (62.9%). Dickey et al [32] have reviewed the literature on a range of office based tools for improving behavioural change counselling in primary care. This included all types of tool, including electronic reminders. They found that no one type of tool or method of teamwork was consistently more effective than another, and identified the need for more high quality research, particularly in the area of health risk assessment and electronic reminder systems.

There is therefore mixed evidence supporting the effectiveness of electronic reminders and a need to confirm their ability to modify clinical behaviour in the particular context of UK primary care under the new GMS Contract.

### Overview of study design

This is a randomised controlled trial to test the effect of an automated electronic feedback system on CVD prevention in general practice. The practice populations over the age of 50 years will be randomised into two groups: "intervention" and "control". Intervention patients currently belonging to one of the high risk search groups described below will have alert messages appear on the screen when their electronic notes are opened. We will also apply an electronic search protocol every eight weeks to both groups throughout the study, to produce continually updated lists of potentially high risk patients for cardiovascular events. For the intervention group the patients on these lists will be revealed to the practice. The clinical software company EMIS, who serve the majority of practices in Warwickshire and Coventry, have programmed their software to produce the alerts and the eight-weekly lists for intervention patients. This "intervention" involves the feedback to practice teams to identify patients who are currently at high estimated risk, patients whose data is incomplete (who may benefit from updated measurements of cholesterol, blood glucose, blood pressure or recording of smoking status) and those who may have undiagnosed diabetes, through the alert messages and the eight-weekly lists. The control group will receive the usual care provided under the nGMS contract. No information will be withheld from the clinicians regarding control patients, the only difference will be the absence of reminders to draw their attention to the information. The practice teams themselves will decide on any changes in treatment in consultation with individual patients in both arms of the study, allowing care to remain tailored at the clinician-patient level. Outcomes will include the number of cardiovascular events and the number of high risk patients in the two populations (defined by inclusion on the eight-weekly search results). The design of the search protocol and the justification for the thresholds are described in the appendix.

## Methods

### Recruitment

Up to twenty-six general practices in Coventry and Warwickshire who use EMIS LV software will be invited to participate in the trial. [name] will visit each practice to explain the trial and gain written consent from the general practitioners.

### Randomisation

Participating practice patients over 50 years of age will be randomised into two groups – "intervention" and "control." Patients will be consistently allocated to these groups throughout the study using an electronic technique that is concealed to all researchers and practitioners involved. This process will occur electronically during each search, so that those who join the practice during the study will be randomised automatically as soon as they are first provided with electronic notes as a fully registered patient. Temporary residents are not included in the study.

### Applying the search strategy

Alerts will be created automatically using patient information that is updated in real time and the search protocol described in Figures 1, 2, 3. For the eight-weekly lists we will apply the same search protocol to the databases of participating practices. This will produce lists for each practice of the high modifiable risk patients in the intervention arm of the study on the day of the search. The groups identified can be summarised as:

**Figure 1 F1:**
[figure not shown]
Search algorithm to identify those most likely to benefit from cardiovascular prevention based on recent risk variable values. Definitions for terms in inverted commas are given in the appendix along with justification of thresholds and search protocol.

**Figure 2 F2:**
[figure not shown]
Identification of Group 5.

**Figure 3 F3:**
[figure not shown]
Identification of Group 6.

GROUP 1: Patients of all ages with existing cardiovascular disease or diabetes, whose blood pressure or cholesterol level is outside the QOF target range at the last estimation, or no "in date" level is recorded.

GROUP 2: Patients who are not known to have cardiovascular disease or diabetes, are *under *75 yrs old, and whose risk profile is incomplete – more information is required to perform a risk estimate – but whose cardiovascular risk would be greater than 20% if the "assumed" values of the missing factors are used (see definition in appendix).

GROUP 3: Patients who are not known to have cardiovascular disease or diabetes, are *under *75 yrs old, and whose most recent risk variable values indicate that their risk level is raised.

GROUP 4: Patients who are not known to have cardiovascular disease or diabetes, are *greater than *75 yrs old and who have persistently elevated blood pressure based on the three most recent consecutive readings.

GROUP 5: Patients with possible undiagnosed diabetes on the basis of at least one previous high blood glucose record.

GROUP 6: Patients with CVD but not diabetes, who have not had a blood glucose measurement in the past three years.

Information on the "intervention" patients identified at each search is revealed to the practices. Information on the control patients including the number identified will be saved but no action will be triggered (Figure 4).

**Figure 4 F4:**
[figure not shown]
Eight-weekly searches on practice databases.

### Intervention – the "e-Nudge"

The e-Nudge is an automated feedback system that examines information already contained in practice databases to help practice teams target preventive interventions towards the individuals most likely to benefit. At the same time, the e-Nudge identifies clinically important missing risk variable values and patients with possible undiagnosed diabetes. Designed to run as a series of updated alert messages and searches that use most recent risk variable values, it is able to track practice populations over time as patients enter and leave the area, grow older, and enter practice disease registers, such as those for diabetes, CHD, or stroke. It recognises that risk profiles are dynamic, and that "one-off" estimates of risk in individuals are liable to become outdated [33].

The alert messages will arise automatically through EMIS software when a high risk patient's notes are opened, and are continuously updated in real time. To identify patients who may not present to the practice, electronic searches will be undertaken every eight weeks. The purpose of both alerts and the lists is to trigger awareness of individual patients' risk within the practice team, and not to dictate specific treatments. The "e-Nudge" is therefore simply the feedback of this information. The resulting action is at the discretion of the practice team, and can be tailored both to the time available, and to the needs and preferences of the individual patient in the context of the clinician's broader knowledge of co-morbidity, current medication, and past response to treatment. The practice teams will have the following notifications for intervention patients identified in the searches.

**1 The eight-weekly search result is presented to a nominated member of the primary care team **under the six group headings.

**2 Alert messages **are displayed automatically on the computer screen each time the patients' electronic notes are opened. These are triggered for those identified in any of the groups:

• Group 1 patients: ***This CHD/Stroke/Diabetes (state which) patient's (BP) or (serum cholesterol) level (specify which) is out of the target range***.

• Group 2 patients: ***This patient may be at high cardiovascular risk, but values for the following risk variables were either missing or out of date: (specify which variables)*.**

• Group 3 patients: ***This patient's estimated cardiovascular risk may be elevated, based on the most recent risk variable values.(State assumptions made)***

• Group 4 patients: ***This patient's blood pressure is persistently elevated based on three consecutive values*.**

• Group 5 patients: ***This patient may have undiagnosed diabetes, based on a previous raised blood glucose level ≥ 11.1 mmol/L***.

• Group 6 patients: ***This CHD/Stroke patient (state which) has no recorded blood glucose measurement in the past three years***.

### Control condition

Control patients at high estimated risk will be identified but the practice teams will not be provided with these extra reminders, although the team will have access to all the clinical information used to assess risk status. Control patients will continue to receive the usual care provided by current general practice under the nGMS contract. Some practices have started to use alerts for CVD or Diabetes patients who are out of the nGMS blood pressure and cholesterol targets since this study was conceived. Where this is now 'usual care,' this part of the intervention (Group 1 alerts) will not be withheld from the control patients, but the rest of the e-Nudge (including identification on the eight-weekly searches) will be. The standard of care is high in the study locality [South Warwickshire Primary Care Trust, QOF data on file], providing a suitable environment to test the e-Nudge. If the study shows a positive effect, this will demonstrate that even good care can be improved, and it is anticipated that the tool will be even more effective in environments where care is of a lower standard.

### Ethical approval

The trial has been developed in accordance with the Declaration of Helsinki, and approved by Warwickshire Local Research Ethics Committee (Ref: 05/Q2803/85).

### Outcome analysis

The searches and alerts will continue for a period of two years, at the end of which the data will be examined. We will continue to collect and analyse data on the primary and secondary outcomes of the study for a further year after this. Outcomes will be measured using searches on practice databases. Analysis will be undertaken on an "Intention To Treat" basis within practices. Practices that withdraw will have their data censored from the date of withdrawal from the trial.

### Primary outcome

Difference in the annual incidence rate of cardiovascular events (see definition in the appendix) in the intervention and control populations during the two years of the study, and for a third year following the end of the e-Nudge intervention.

### Secondary outcomes

• Difference in the proportion of high risk patients (Groups 1, 3 and 4) identified in the control and intervention populations averaged over the last three searches in the two year intervention period, and in the third year following the end of the intervention.

• Difference in the proportion of patients in each population identified with missing data (Groups 2 and 6) averaged over the last three searches in the two year intervention period, and in the third year following the end of the intervention.

• Difference in the proportion of patients with undefined diabetes status (i.e. raised blood glucose levels with no diagnosis of diabetes and no FBG or OGTT results to confirm status) (Group 5) in the intervention and control populations averaged over the last three searches in the two year intervention period, and in the third year following the end of the intervention.

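### The high-risk secondary outcome (Groups 1, 3 and 4) can rise or fall with data completeness alone, so a difference between arms cannot be read as a change in risk

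*Protocol article*

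**What the plan says.** Under Secondary outcomes, the protocol article fixes two pooled proportions that matter here. One is the "Difference in the proportion of high risk patients (Groups 1, 3 and 4) identified in the control and intervention populations". The other is the "Difference in the proportion of patients in each population identified with missing data (Groups 2 and 6"). Each is averaged over the last three searches of the two-year intervention period and assessed again in the third year.

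The groups are defined under Applying the search strategy:

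- **Group 1** is drawn from patients who have diabetes or CVD and is limited to those "whose blood pressure or cholesterol level is outside the QOF target range at the last estimation, or no 'in date' level is recorded"; either ground is enough for entry.
- **Group 2** holds patients under 75 without either condition "whose risk profile is incomplete" on the data held, "but whose cardiovascular risk would be greater than 20% if the 'assumed' values of the missing factors are used".
- **Group 3** holds patients under 75 without either condition "whose most recent risk variable values indicate that their risk level is raised".

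The Overview of study design makes high-risk status a matter of being on the eight-weekly search list. It also names patients with incomplete data as a target of the feedback. Under Control condition, controls do not receive the reminders, with one exception: in practices that already use such alerts, "this part of the intervention (Group 1 alerts) will not be withheld from the control patients". The eight-weekly lists are still withheld from controls in those practices.

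**The concern.** The outcome is named as a measure of high risk but is built from lists whose membership depends on what has been recorded. Two features cause the difficulty.

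First, Group 1 is counted wholly as high risk, although some of its members are there only because "or no 'in date' level is recorded". They are missing-data patients who appear in the high-risk outcome and not in the missing-data outcome.

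Second, Groups 2 and 3 can hold the same patient before and after measurement. Someone measured because of a Group 2 alert and found to be at raised risk leaves the missing-data outcome and enters the high-risk outcome, with no change in true risk.

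Better recording is one of the things the alerts are meant to achieve, so completeness will differ by arm if they work. A real fall in risk could then be hidden or reversed in the pooled figure, and a pure recording effect could look like benefit.

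**Working it through.** The document states no sample size, expected proportion or group size for this outcome. Its only sample-size figure concerns the primary outcome, so there is no figure to reproduce. The check traces moves between groups while every patient's true risk is held fixed.

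**Moves when a missing value is filled**

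| Starting point | Result once measured | High-risk outcome (1, 3, 4) | Missing-data outcome (2, 6) |
|---|---|---|---|
| Group 2 | Risk raised: enters Group 3 | up | down |
| Group 2 | Risk not raised: enters no group | unchanged | down |
| Group 1, flagged only for a missing value | Out of target: stays in Group 1 | unchanged | unchanged |
| Group 1, flagged only for a missing value | In target: leaves Group 1 | down | unchanged |

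The second row is a real possibility. Appendix 5c assumes positive diabetes status where glucose is missing, so a normal result can take a patient below the threshold.

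**Formula.** Let, per 1000 patients, *G2* be the size of Group 2 and *M1* the number in Group 1 flagged only for a missing value. Let *r* be the share of Group 2 found to be at raised risk, *q* the share of *M1* found out of target, and *f* the extra fraction of gaps filled in the intervention arm. Then

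change in Groups 1, 3 and 4 = *f* × [*G2* × *r* − *M1* × (1 − *q*)].

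**Numbers.** All inputs are assumptions: *f* = 0.5; *G2* = 20, 50 or 100; *r* = 0.2, 0.4 or 0.6; *M1* = 10, 30 or 60; *q* = 0.2, 0.4 or 0.6. That gives 81 combinations.

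- *G2* = 100, *r* = 0.4, *M1* = 30, *q* = 0.4: 0.5 × (40 − 18) = +11 per 1000.
- *G2* = 50, *r* = 0.4, *M1* = 30, *q* = 0.4: 0.5 × (20 − 18) = +1 per 1000.
- *G2* = 20, *r* = 0.4, *M1* = 60, *q* = 0.4: 0.5 × (8 − 36) = −14 per 1000.
- Lowest: *G2* = 20, *r* = 0.2, *M1* = 60, *q* = 0.2: 0.5 × (4 − 48) = −22 per 1000.
- Highest: *G2* = 100, *r* = 0.6, *M1* = 10, *q* = 0.6: 0.5 × (60 − 4) = +28 per 1000.

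The count rises in 42 combinations, falls in 36 and is unchanged in 3.

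**Scale.** Assume that 35% of the 70,000 list is over 50, so 12,250 per arm, and that the baseline proportion is 20%. The standard error of the difference is √(2 × 0.2 × 0.8 / 12,250) = 0.0051, or about 5 per 1000. A shift of the size shown could therefore exceed sampling error, but it could also be close to nil.

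**Diabetes route.** A Group 5 patient confirmed as diabetic becomes eligible for Group 1. Table 2 in Appendix 2 and the text after it report 6 such patients among 12,245 registered, 4 of them confirmed. Scaled up, 4 × 70,000 / 12,245 ≈ 23, or about 11 per arm. On 12,250 per arm that is about 0.1%, even if all were over 50 and out of target, and so under a fifth of the standard error.

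**The case against.** A reader might infer that the outcome must rise when the alerts succeed in filling gaps. The definitions do not support that. Filling a gap in Group 1 can only keep the patient there or remove them, and some Group 2 patients leave every group once measured.

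A reader might also count the Group 2 to Group 3 flow alone. If Group 2 is 5–10% of patients, 20–40% more are measured and 20–40% prove high risk, the rise is 0.2 to 1.6 percentage points, and the top is about 3 standard errors. That takes the top of three assumed ranges and omits the Group 1 offset. The midpoints give 7.5% × 30% × 30% ≈ 0.68 points, about 1.3 standard errors before any offset. Newly detected patients also trigger Group 3 alerts and may have left the group by the last three searches.

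Other points on this side have weight:

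- Calling Group 1 high risk is defensible, since Appendix 4 treats these patients as secondary prevention. The Abstract describes the missing-data outcome as concerning a risk estimate, which they do not need. But Group 6 patients, who have cardiovascular disease, do not need one either and are counted there.
- Figure 1 is not shown, and the Group 3 alert has a place for assumptions made, so the boundary between Groups 2 and 3 may be less clean than the text suggests.
- Shared Group 1 alerts occur only in some practices, and the lists remain withheld from controls there. Dilution in Group 1 is partial.
- The missing-data outcome is reported alongside, and reporting by group could be left to an analysis plan.

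The last point does not remove the problem, because the Secondary outcomes section itself fixes which groups are pooled. An analysis plan that follows it inherits the mixture.

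**Conclusion.** The point holds for one secondary outcome. As defined, the pooled proportion in Groups 1, 3 and 4 responds to completeness as well as to risk, and the intervention is designed to change completeness in one arm, apart from the shared Group 1 alerts in some practices. Neither a difference between arms nor its absence can be read as a change in risk.

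That Group 1 mixes out-of-target and missing values follows directly from its definition. The Group 2 to Group 3 move rests on the text definitions, without sight of Figure 1. The direction and size of the net effect are unknown: −22 to +28 per 1000 is an illustration on assumed sizes, not an estimate. The diabetes route is negligible on the document's own pilot figures.

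It would go too far to infer that the trial cannot show a benefit. The primary outcome counts cardiovascular events and is unaffected, and separate reporting of the groups would recover much of what the pooled figure hides. This should be changed, but it does not threaten the main result.

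**What to change.** 1. Split Group 1 into 1a (a recorded value out of target) and 1b (flagged only because no in-date value exists). Count 1b with the missing-data outcome. Report Groups 1a, 1b, 2, 3 and 4 separately by arm beside the pooled figure.
2. Add an analysis of patients in Group 1a, 3 or 4 at the first search, using the same search in both arms: the proportion still high risk over the last three searches. A value that lapses out of date (fifteen months or three years, Appendix 5a) must not count as resolved, so carry the last value forward. Otherwise poor recording would look like benefit.
3. Report Groups 2 and 3 together as a supporting figure. Moves between them cannot alter it. Note that it can still fall through recording alone, because Group 2 assumes positive diabetes status.
4. Report Group 1 by whether controls in the practice also receive Group 1 alerts.

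The cost is a change of outcome wording and a few extra tabulations from searches already run in both arms. The cohort analysis in item 2 leaves out patients who join later, whom the Randomisation section includes by design. It should therefore supplement the whole-population figure, not replace it.
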